##### Compositional Data

Compositional data analysis has been suggested to examine movement behaviors occurring within a finite period, specifically when they are continuously measured using accelerometers (31). The time spent on one movement behavior relative to all other behaviors will be presented as isometric log-ratio coordinates (*ilr*), which will be the outcome variable in the regression models. For example, a 24-h period can be divided into time spent in PA, SB, and sleep. Taking PA as an example, the equation is as follows:

$$\begin{array}{l} ilr_{1}=\sqrt{\frac{2}{3}}\ln\left(\frac{PA}{\sqrt[{2}]{SB^{*}Sleep}}\right) \end{array}$$

where *ilr*_1_ represents sleep relative to all other movement behaviors.

The time allocated to SB relative to other movement behaviors can be assessed using the *ilr*_2_, which can be expressed as follows:

$$\begin{array}{l} ilr_{2}=\sqrt{\frac{2}{3}}\ln\left(\frac{SB}{\sqrt[{2}]{PA^{*}Sleep}}\right) \end{array}$$

Similarly, the time allocated to sleep relative to other movement behaviors can be assessed using *ilr*_3_, which can be expressed as follows:

$$\begin{array}{l} ilr_{3}=\sqrt{\frac{2}{3}}\ln\left(\frac{Sleep}{\sqrt[{2}]{PA^{*}SB}}\right) \end{array}$$

##### Children's Physical Activity and Sedentary Behavior

ActiGraph accelerometers (ActiGraph, Pensacola, Florida, USA) will be used to assess children's PA and sedentary time. During a school visit, trained researchers will help children attach the ActiGraph to their non-dominant wrist using a wrist band (32). Children will be asked to wear the device for seven consecutive days during 24-h period. The ActiGraph should be removed when children undertake any water-based activities (e.g., bathing and swimming), and parents will be asked to complete a log sheet to record the time and reasons for removing the device. The ActiGraph data will be collected at a sampling rate of 30 Hz (32). Data will be downloaded using ActiLife software v6.13.4. and analyzed in 5-s epochs. A time period of more than 60 min of zero counts continuously will be regarded as non-wear time. Days with at least 16 hours recorded as wearing time will be regarded as valid (33). To reflect children's habitual behavior patterns, only children who provide data for at least 3 days including at least 1 weekend day will be included in the final analysis (34). Cut-off points that have been validated in preschool-aged children will be used. Specifically, sedentary time, LPA, and MVPA will be defined as ≤ 328 counts, 329–1392 counts, and ≥1393 counts per 5 seconds for vector magnitude, respectively (32). Total PA (TPA) will be calculated by summing LPA and MVPA.

##### Children's Screen Time

Screen time will be reported by parents using a question modified from the Children's Leisure Activities Study Survey questionnaire–Chinese version (CLASS-C) (35): How much time does your child spend on sedentary screen time (e.g., watching TV/DVDs, playing video games, using computers, using tablets and mobile phones)?

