Three online workshops delivered as Zoom meetings will be held for parents in the intervention groups in weeks 1, 3, and 6. The workshops will aim to explain strategies that can be adopted by parents based on BCTs and TPB to solve problems and to encourage parents to comply with the intervention. Specifically, the first workshop will be a brief lecture for parents about the 24-h movement guidelines and the association between movement behaviors and health outcomes, as well as a general introduction to the program (e.g., how to set individual goals, how to use the materials). The second and third workshops will focus on discussing and providing strategies to overcome barriers that the parents have experienced during the intervention, as well as strategies to develop habits. Each workshop will be held as a group meeting of approximately 10 parents to ensure manageability and feasibility. Activities such as check-in polls, topic-based Q & A sessions, and breakout rooms for small-group discussions will be designed to facilitate the workshops. Each workshop will last for 30 to 45 min. If any parents do not have time to attend the workshops, a recorded video of the workshop will be sent to them, and a phone call will be made to provide a brief introduction to the workshop, ask whether they have had any challenges, and suggest strategies. Every 2 weeks, the parents will be asked to complete an online questionnaire using Google Forms. The questions will relate to the children's movement behaviors (e.g., average PA, SB, screen time, bedtime, and wakeup time), whether and how they have used the planning materials for each movement behavior, whether they have achieved the goals and schedules for the coming 2 weeks, etc. At the end of each questionnaire, reminders about the materials use will be presented.

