	Week 9 & 10	Planning, habit development	Action planning (1.4) Behavioral substitution (8.2) Habit formation (8.3)	1. Examples of improving physical activity, reduce sedentary behavior, and improve sleep 2. Strategies for developing habits (substitution, repetition)
	Week 11 & 12	Monitoring, habit development	Feedback on behavior (2.2) Behavioral substitution (8.2) Habit formation (8.3)	1. Individual report on the change of children's movement behaviors during the past 10 weeks (based on parent-reported interactive questionnaires) 2. Strategies for developing habits (substitution, repetition)
Workshops	Week 1	Subjective norm, attitude toward the behavior, goal setting	Information of others' approval (6.3) Information about health consequences (5.1) Goal-setting (behavior) (1.1)	1. Introduction of the program 2. WHO 24-h movement guidelines for preschoolers 3. Benefits of having a healthy lifestyle (i.e., high PA, low SB, low screen time, sufficient sleep) for preschoolers 4. Steps and strategies of goal setting
	Week 3	Perceived behavioral control, intention	Problem-solving (1.2) Verbal persuasion about capability (15.1)	1. Solve problems that families have faced using materials 2. Provide strategies to parental perceived barriers 3. Sharing experiences 4. Encouraging families to comply with the intervention
	Week 6	Perceived behavioral control, intention, habit development	Problem-solving (1.2) Verbal persuasion about capability (15.1) Habit formation (8.3)	1. Provide strategies to parental perceived barriers 2. Sharing experiences 3. Encouraging families to comply with the intervention 4. Example of habits 5. Strategies for developing habits
Interactive questionnaires	Week 2, 4, 6, 8, & 10	Goal setting, monitoring	Review behavior goals (1.5) Self-monitoring of behavior (2.3)	1. Movement behaviors over the past two weeks (duration, whether achieve the goal or not) 2. Bi-weekly goals for each movement behavior 3. Reminders of materials use

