### Outcomes

#### Primary Outcomes

##### Activity Sleep Index

Similar to the activity-sleep index created for adults (27), a composite movement behavior score will be created to summarize the multiple dimensions of PA, SB, and sleep among preschoolers. The composite movement behavior score will comprise scores for the following six dimensions representing broad variables that have been examined in relation to the 24-h movement guidelines (28, 29) and in previous studies on sleep among young children (30):

PA: total time on PA of all intensities.PA: total time on MVPA.Screen time.Sleep: bedtime duration (time in bed).Sleep: sleep onset variability (variability in sleep onset times).Sleep: morning wake-time variability (variability in wake times).

Each item will be rescaled from 0 to 10, with a higher score indicating healthier movement behaviors. The formula for rescaling is as follows (27):

$$\begin{array}{l} Rescaled\;score\;=\;\left(\frac{\left(X-X_{\min}\right)}{X_{Range}}\right)\times 10 \end{array}$$

where *X* is the observed value, *X*_min_ is the minimum value observed, and *X*_range_ is the difference between the maximum and minimum values observed (27). A total score ranging from 0 to 60 will be obtained by summing the scores for all items, with higher scores indicating healthier movement behaviors.

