### Randomization and Blinding

Randomization and group assignment will be conducted using computer-generated random numbers by a third person who is blinded to the purpose of the study. After baseline data collection, the participants will be randomly allocated to one of three arms. The trained staff who will be responsible for data collection will also be blinded to group assignment. Although blinding participants to the intervention is not feasible for this study, families in the two intervention groups will not be disclosed of the differences in the intervention contents.

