### Statistical Methods

Analyses will be performed using SPSS 27.0. The significance level will be set at 0.05. Descriptive statistics will be presented for the children's baseline movement behaviors. Feasibility and acceptability will be presented using percentages. Differences in movement behaviors across three groups at baseline will be assessed using analysis of covariance. The intention-to-treat principle (all participants) and sensitivity analysis (participants with complete data) will be used to compare primary outcomes between groups. Generalized estimating equations will be applied to examine the effects of the intervention (PA + SB group vs. control group, PA + SB + sleep group vs. control group) on primary outcomes (children's overall movement behaviors, total PA, MVPA, sedentary time, screen time, sleep duration) and secondary outcomes, adjusting for covariates. Also, the difference of the effect between two intervention groups (PA + SB group vs. PA + SB + sleep) will be examined using generalized estimating equations.

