Through this intervention, we will also aim to help parents develop a healthier lifestyle. Evidence from a systematic review suggests that there are small but positive associations between parents' and children's movement behaviors, based on a majority of cross-sectional studies (51). A consensus statement on the importance of the family to the movement behaviors of children and youth noted that parents can support their children by improving their lifestyles in various ways, including modeling and co-participation (16). An ongoing 6-month-intervention that aims to increase children's PA will evaluate parents' PA, but no results are available yet (52). Thus, there is a need to explore the changes in parents' movement behaviors after our proposed interventions. We hypothesize that parents in the intervention groups will improve their movement behaviors.

The proposed study has numerous strengths, including targeting all three 24-h movement behaviors, the application of a theoretical framework, objective measurement of children's movement behaviors, and an RCT design. The proposed intervention is parent-focused and will explore an integrated approach targeting all three movement behaviors for preschool-aged children. The findings will help to determine best practices for behavior change. The beneficiaries will include families with young children and other stakeholders in early education.

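### Screen time, a primary outcome and one of six activity sleep index items, rests on one question to unblinded parents whom the intervention conditions differently from controls, so reporting differences can appear as an effect against control

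*Protocol article*

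**What the plan says.** All references are to the protocol article.

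- **Status.** Statistical Methods lists screen time among the "primary outcomes (children's overall movement behaviors, total PA, MVPA, sedentary time, screen time, sleep duration"), with no order of importance. It also enters the Activity Sleep Index: "The composite movement behavior score will comprise scores for the following six dimensions", and "Each item will be rescaled from 0 to 10, with a higher score indicating healthier movement behaviors", giving a total of 0 to 60.
- **Source.** Children's Screen Time: "Screen time will be reported by parents using a question modified from the Children's Leisure Activities Study Survey questionnaire". No device or other check is described.
- **Blinding.** Randomization and Blinding: "Although blinding participants to the intervention is not feasible for this study". Data collectors are blinded, and the two active arms are not told how their content differs.
- **Active arms.** PA + SB Group describes materials aimed at screen time among other behaviors, a schedule with biweekly goals for each movement behavior, and a questionnaire every two weeks: "The questions will relate to the children's movement behaviors (e.g., average PA, SB, screen time, bedtime, and wakeup time"). Table 1 places these questionnaires in weeks 2, 4, 6, 8 and 10. For weeks 11 and 12 it lists: "Individual report on the change of children's movement behaviors during the past 10 weeks (based on parent-reported interactive questionnaires"). Table 1 describes the integrated arm; the accompanying text gives the dyadic arm the same strategies without the sleep content.
- **Control arm.** Wait-List Control Group: no intervention, and the materials only after follow-up.
- **Timing.** Procedure puts T3 at 12 weeks. It also says that parents get a brief report after baseline and mid-term, without limiting this to an arm.
- **Claim.** The Discussion lists "objective measurement of children's movement behaviors" as a strength, without excepting screen time.

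**The concern.** Parent report by unblinded parents is a common limitation. Here the design adds to it, because the person who supplies the outcome is conditioned differently by arm. Active-arm parents have been told that less screen time is healthier, have worked with goals, have been asked about screen time up to five times, and are shown the trend in their own answers at about the time of the T3 question. Controls have none of these four elements.

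All of this happens after randomization, so adjusting for baseline cannot remove it. Blinded data collectors do not help either, because the answer comes from the parent.

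Hypothesis 2 is that both approaches change behavior. Because screen time stands beside the accelerometer outcomes with no ranking, a difference from control on screen time could be offered by itself as support for that hypothesis, and it could be a difference in reporting only.

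**Working it through.** **1. The plan's own figure.** Sample Size gives 99 (33 per group) for f = 0.15, power 0.90, alpha 0.05, three arms, four measures and correlation 0.50. For a within-between interaction, lambda = f² × N × m / (1 − rho) = 0.0225 × 99 × 4 / 0.50 = 17.82, with df1 = 2 × 3 = 6 and df2 = 96 × 3 = 288. Power is 0.9003, so 99 reproduces. The trial is thus designed around a small effect, and a small bias is not negligible beside it.

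**2. Numbers per arm.** 150 / 3 = 50. With the stated 20% attrition, 50 × 0.8 = 40.

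**3. Size of the reporting shift (assumption).** The documents give neither an SD for screen time nor a bias size. For scale, the Introduction cites a 30.6 min/day reduction for family-based interventions. Assume that reporting alone moves the answer by about half of that, 15 min/day. Assume also an observed range of 180-360 min and an SD of one fifth of the range, 36-72 min:

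- 15 / 72 = 0.21 SD
- 15 / 36 = 0.42 SD

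**4. Chance of a significant screen-time result with no true effect.** One visit, two groups, no adjustment: SE = √(2/n) in SD units, and P = Φ(b/SE − 1.96) + Φ(−b/SE − 1.96).

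| n per arm | b = 0.21 SD | b = 0.42 SD |
|---|---|---|
| 40 | 0.15 | 0.46 |
| 50 | 0.18 | 0.55 |

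The nominal rate is 0.05. Baseline adjustment makes the biased contrast more precise without correcting it: for a 0.3 SD shift at 40 per arm, P is 0.27 unadjusted and 0.34 adjusted with correlation 0.50.

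**5. Effect on the index.** The nominal weight of screen time is 10 / 60 = 1/6; the real weight depends on each item's spread after rescaling. A 15-minute shift moves the item by 15/360 × 10 = 0.42 to 15/180 × 10 = 0.83 points. Assume an item SD of 2 and a pairwise correlation of 0 to 0.2:

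- index SD at correlation 0: √(6 × 4) = 4.9
- index SD at correlation 0.2: √(24 + 30 × 0.2 × 4) = 6.9
- shift: 0.42 / 6.9 = 0.06 SD to 0.83 / 4.9 = 0.17 SD

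At 50 per arm this gives a false-positive rate of about 0.06-0.14. It presumes that the screen item is reversed so that higher means healthier. The printed rescaling formula shows no reversal; taken literally, under-reporting would lower the index.

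**6. Which contrasts are exposed.** The two comparisons with control are exposed. Both active arms get the same screen content and prompts, so the bias should largely cancel in PA + SB versus PA + SB + sleep. Total PA, MVPA and sedentary time come from the accelerometer. Sleep is only partly exposed, through matching with a parent diary.

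**The case against.** The strongest reply is that the article discloses both the parent report and the lack of blinding, that nothing is miscalculated, and that sensitivity analyses for bias are usually left to the analysis plan. Disclosure does not remove the problem, however. The outcome, its source and the feedback component are fixed in this document, and an analysis cannot undo a report seen before the question is answered.

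Several limits do stand:

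- A reader might infer that control parents get no feedback at all. The text does not support that. The brief reports after T1 and T2, with the gap from recommended durations, go to parents without limit by arm. The feasibility section counts two brief reports under intervention fidelity, so who receives them is unclear.
- A reader might infer that the trend report certainly arrives just before T3 and makes the bias worst there. Table 1 says only weeks 11 and 12 and gives no send date, and nothing shows how the bias compares with that at T2 or T4.
- The wording of the biweekly screen question is not given, so it cannot be called the same question. Specific screen-time goals are a plausible reading of goals for each movement behavior, but are not stated.
- Every magnitude is an assumption, and the single-visit comparison is not the planned generalized estimating equations.
- Screen time is a targeted behavior and is named in the WHO guideline, so keeping it as a primary outcome is defensible.
- The Discussion elsewhere ties device-based measurement to the compositional outcome, which contains no screen time. The strengths sentence is therefore loose rather than misleading by design.

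**Conclusion.** The point holds as a design weakness confined to the comparisons with control. For screen time analysed alone, a reporting shift of about 0.2-0.4 SD would turn a nominal 5% error rate into roughly 15-55% at 40-50 per arm at one visit. That range rests wholly on the assumed shift and SD. For the index the contamination is small, about 0.06-0.17 SD, and acts in the stated direction only if screen time is reverse-scored.

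A stronger reading would be that the effectiveness conclusion as a whole, or the test of the integrated against the dyadic approach, is compromised. The documents do not support this. The accelerometer outcomes are not open to this bias, and the two active arms share the same screen content. The point is an inexpensive improvement that the plan should adopt.

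**What to change.** 1. Add a sensitivity version of the activity sleep index without the screen item (five mainly accelerometer-derived items, 0-50), and report whether the index conclusion against control holds on it.
2. State that a difference from control on parent-reported screen time alone will not support the effectiveness conclusion unless the accelerometer-derived primary outcomes also support it. Screen time can stay a primary outcome.
3. In the Discussion, limit the objective-measurement claim to PA, sedentary time and, with the diary matching acknowledged, sleep.
4. Reconcile the order of the T3 screen-time question and the weeks 11-12 report, for example by collecting the questionnaire before parents see the report. The component itself need not be removed.

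The cost is protocol wording, one extra derived score, a check on the order of two contacts, and a slightly narrower claim for screen time. No extra participants or visits are needed.

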##### Children's Sleep Duration

Sleep duration will be assessed using ActiGraph data matched with a parent-reported diary and nap schedule provided by kindergartens. The duration of nighttime sleep will be estimated using ActiLife software v6.13.4 in 60-s epochs. The automated Sadeh et al. algorithm (36) will be applied to identify bedtime and wakeup time, and the Tudor-Locke algorithm (37) will be used to detect periods of sleep. For the duration of daytime naps, bedtime and wakeup time will be identified using ActiLife software and matched with the nap schedule provided by kindergartens and log sheets completed by parents. The total sleep duration in a day will be defined as the sum of nighttime sleep and daytime naps.

#### Secondary Outcomes

##### Children's Sleep Quality

Children's sleep quality will be measured using the Chinese version of the Children's Sleep Habits Questionnaire (CSHQ) (38), which has been used to measure Chinese preschoolers' sleep patterns and problems based on parental reports. The CSHQ consists of 33 items in eight dimensions: bedtime resistance, sleep onset delay, sleep duration, sleep anxiety, night waking, parasomnias, sleep-disordered breathing, and daytime sleepiness. Three options are provided for each item: 5 to 7 times a week (scored 3), 2 to 4 times a week (scored 2), and 0 to 1 time a week (scored 1). Higher scores indicate greater sleep problems. The Chinese version of the CSHQ has shown good reliability (Cronbach's α = 0.73) and validity (38).

##### Children's Body Mass Index

Preschoolers' heights and weights will be measured by trained researchers during school visits. Children's body mass index (BMI) will be calculated as weight (kg)/height (m^2^).

##### Parents' Physical Activity and Sedentary Behavior

The Chinese version of the International Physical Activity Questionnaire–Short Form (IPAQ-SF) (39) will be used to estimate parents' PA (walking, moderate-intensity PA [MPA], vigorous-intensity PA [VPA], total energy expenditure) and SB over the previous seven days. Energy expenditure corresponding to walking, MPA, and VPA are 3.3 metabolic equivalents (METs), 4.0 METs, and 8.0 METs, respectively. The sum of energy expenditure on walking, MPA, and VPA will be considered total energy expenditure (MET-minutes/week).

##### Parents' Screen Time

Parents will respond to two questions: (1) on average, in a 24-h day, how much time do you usually spend on sedentary screen time (e.g., using computers, tablets, and mobile phones) for work, and (2) how much time do you usually spend on sedentary screen time (e.g., watching TV/DVDs, playing video games, using computers, using tablets, and mobile phones) for leisure and entertainment?

##### Parents' Sleep Duration and Quality

Parents' sleep duration and quality over the previous month will be measured using the Chinese version of the Pittsburgh Sleep Quality Index (PSQI) (40). The PSQI consists of 18 self-reported items in seven dimensions: sleep quality, sleep latency, sleep duration, habitual sleep efficiency, sleep disturbance, sleep medication used, and daytime dysfunction. Four options scored from 0 to 4 are provided for each item and a higher PSQI score indicates worse sleep quality. The PSQI has shown good reliability (Cronbach's α = 0.84) and validity among Chinese adults (40).

